## Final Study Visit (Day 168)

The final study visit will include:

- Confirm participant identify and study number.
- Administer questionnaire reviewing changes in medical history since the last visit.
- Record adverse events as reported by subject or observed by investigator.
- Measure and record vital signs, including:
  - Child’s height, weight and MUAC
  - Child’s axillary temperature
- Have 3–4 mL of blood drawn by venous phlebotomy from the child to:
  - Perform testing for hemoglobin concentration
  - Create dried blood spots (DBS) for qPCR testing at a later date.
  - Store sera for future seroprevalence studies of vector-borne disease
- Have 6–8 mL of blood drawn by venous phlebotomy from the mother to:
  - Perform testing for Hb concentration
  - Create DBS for qPCR testing at a later date.
  - Store sera for future seroprevalence studies of vector-borne disease
- Obtain punch from *lesus* to measure permethrin content.
- Complete semi-structured exit interview.
- Provide study completion incentive of approximately $20.

## Unscheduled Visits

Participants will be instructed to present to their respective study clinic for any acute febrile illness or other symptoms that may be consistent with malaria (e.g., poor feeding, headache, malaise). Upon registration, participants will present their study ID card to health center staff, who will subsequently notify study staff of the visit. Participants will undergo routine evaluation, testing, and treatment in accordance with local protocols. At the conclusion of the visit, a staff member will interview the patient to document symptoms and review clinic and laboratory registers to abstract relevant information. Of note, the study will maintain a modest supply of RDTs and artemether-lumefantrine (AL) to ensure there is no shortage of diagnostic tests or treatment.

# STUDY PROCEDURES /EVALUATIONS

## Study Procedures/Evaluations

### Demographic and Medical History

During the household visit, staff will record the full name, date-of-birth, sex, educational history, occupation, and other demographic characteristics of the participant and child. Relevant medical history collected will include obstetric (or birth) history, current diagnoses and medications, and any history of hospitalizations. At subsequent visits, staff will enquire about interval history (i.e., previous 2 weeks) including (i) the presence of any symptoms consistent with malaria (e.g., fever, headache, lethargy, poor-feeding, diarrhea), (ii) care-seeking in the public or private sector, (iii) treatments received, and (iv) potential adverse reactions to the intervention.

### Household

Study staff will record the location of the household using a handheld GPS device and administer a questionnaire modified from the most recent Demographic and Health Survey [21] covering topics including:

- The age, sex, and relationship to the participant of each household member
- Name of the CHW responsible for the household
- Household characteristics (e.g., rooms, materials, water sources, toilet, etc.)
- Indices of socioeconomic status including ownership of items such as a cell phone, motorcycle, etc.
- Malaria knowledge, care-seeking patterns, and prevention behaviors

### Physical examinations

Study staff will measure vital signs including height, weight, MUAC, and axillary temperature at each visit. A clinical officer will perform a general physical examination, including full inspection of the skin, of all participating children at the baseline visit. At subsequent visits, a clinical officer will be available to perform focused clinical assessments, but only in response to adverse events reported by participants or staff.

### Biological specimens

Trained study staff trained will perform all blood collection procedures in accordance with established methods and study-specific standard operating procedures. Blood collection at the baseline (Day 0), mid-point (Day 84), and final visits will be performed by venous phlebotomy with the goal of collecting 7–8 mL of whole blood from mothers and 3–4 mL from children. Aliquots of whole blood will be removed from the vacutainer by pipette for point-of-care testing and creation of DBS. Remnant blood will be processed for long-term storage (see Section 7.2.3). All other collections will be capillary blood specimens obtained by finger- or heel-stick with the goal of obtaining approximately 50 µL.

### Self-reported data

Participants will be asked to keep daily logs (“diaries”) documenting the frequency of:

- Mother and child sleeping under LLIN
- *Lesu* use throughout day, divided into morning, afternoon, and evening
- *Lesu* washing

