In pursuit of this goal, we sought to leverage the traditional practice of mothers carrying young children on their backs utilizing wraps made from locally purchased cloth (**Figure 1**). The wrap, called a *lesu* in Uganda, also serves as a blanket or swaddle for children when they are put down or put to bed. Thus, mother and child spend much of the day in contact with the cloth. We hypothesized that when treated with an insecticide or repellent, the *lesu* might provide an additional layer of protection against malaria. A similar intervention has been shown effective for preventing mosquito and tick bites among outdoor workers in the Southeastern United States [19, 20]. Our approach has many potential advantages including: (i) targeting the most vulnerable (i.e. young children), (ii) integrating with existing cultural norms, and (iii) complementing current prevention strategies by offering protection against outdoor- and/or day-time biting *Anopheles* mosquitoes.

**Figure 1:** Ugandan mother carrying her child in a *lesu*.

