Every two weeks, participants attended study visits where clinical staff assessed mothers and infants for adverse reactions and performed testing for malaria using a malaria RDT. Research staff administered a brief questionnaire of recent medical history (e.g., rash, fever), care-seeking, and frequency of *lesu* use and washing. We also measured the child’s mid-upper arm circumference (MUAC), a validated tool for assessing nutritional status [22] and Hb levels at the initial and 12-week visits. At study completion, participating mothers completed a semi-structured interview eliciting perceptions of safety and effectiveness. Study procedures were approved by the University of North Carolina Institutional Review Board (18-1819), the Mbarara University of Science and Technology Research Ethics Committee (05/08-18), and the Uganda National Council of Science and Technology (SS 4833).

A total of 48 of 50 mother-infant pairs completed study activities. Two participants only completed baseline activities and replacements were subsequently recruited bringing the total to 50 participants. Overall, caregivers had relatively low educational attainment, multiple children in the home, and limited resources, although these characteristics were generally well-balanced between the groups. Almost all mothers reported using the *lesu* to carry the child on their back, while about one-third (n=17, 34%) also reported using the *lesu* as a blanket to put the child down to sleep.

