### Observation logs

Study staff will perform direct observation of a random sample of participants (25%) to document how and when *lesus* are used throughout the day with particular emphasis on the morning and evening periods. Staff will also enquire how participants wash the *lesus* and confirm that LLINs are being used.

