## Final Analysis Plan

Analyses will be conducted using an ITT approach, with woman-infant pairs analyzed according to the arm they were randomly assigned to (i.e., treated or untreated *lesu*) regardless of their subsequent use or non-use of the *lesus* and dropout. *Lesu* use will be evaluated as a secondary outcome, and if *lesu* use is lower than anticipated, exploratory analyses may use marginal structural models to estimate an “as-treated” effect of permethrin-treated *lesus* on the primary endpoint.

An α=0.05 significance level will be used throughout, with corresponding 95% confidence intervals. No adjustment for multiple testing will be made for the primary outcome. For secondary outcomes (excluding safety endpoints), we will control the false discovery rate using methods from Benjamini and Hochberg (1995).

Given the level of subject participation in the pilot study, we expect most mother-infant pairs to complete all study activities. Missing data due to dropout or missed clinic visits are anticipated to be uncommon (≤5% missing), so a complete case analysis is planned. If >10% of participants are missing data in either arm, a sensitivity analysis will be conducted using multiple imputation assuming data are missing at random (missing conditional upon measured baseline covariates and study outcomes). If data are suspected to be missing not at random, this will be described with the study results as a limitation.

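### The daily diary has no night or sleep entry for lesu use, although the protocol describes the cloth as bedding, so no source whose content the protocol describes records overnight contact

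*Protocol*

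**What the plan says.** Protocol section 7.1.5 (Self-reported data) lists three diary items:

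- net use, worded as "Mother and child sleeping under LLIN";
- lesu "use throughout day, divided into morning, afternoon, and evening";
- lesu washing.

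Sleep therefore appears only for the net.

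The protocol also describes the cloth as bedding. Section 1.1 (Background Information) says that it "also serves as a blanket or swaddle for children when they are put down or put to bed". Section 1.2 (Pilot Study) reports that about a third of mothers used it "as a blanket to put the child down to sleep".

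Section 2.2 lists the frequency of lesu use and washing as covariate 4.C, with three sources: the bi-weekly questionnaire, the diaries and direct observation. Observation is described in sections 5.9 and 7.1.6. It takes place during the day, "with particular emphasis on the morning and evening periods", in a 25% random sample.

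Section 10.3 says that lesu use will be evaluated as a secondary outcome. It adds that, if use falls short of expectation, "exploratory analyses may use marginal structural models" to estimate an as-treated effect on the primary endpoint. Section 10.3.1 adds exploratory Poisson models of malaria incidence on lesu use, washing and residual permethrin. The primary analysis is by intention to treat.

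**The concern.** The diary is the only daily record of lesu use described for every pair, and its periods leave out a use that the protocol itself reports. A mother whose child sleeps under the cloth all night has no entry in which to say so. An evening entry may record that the cloth was in use at bedtime, but not whether it stayed with the child overnight.

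The error runs in one direction: leaving out night use can only lower recorded use. Three planned uses of the measure are exposed:

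- The lesu-use secondary outcome may understate use.
- The as-treated model is triggered by low use and takes use as its exposure, so both the decision to run it and the classification within it can be wrong.
- In the exploratory use models, a child covered nightly but with little daytime use is placed among the low users.

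Contact that is not recorded during follow-up cannot be reliably recovered afterwards.

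**Working it through.** **Inputs**

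- Diary periods: morning, afternoon, evening (section 7.1.5).
- Pilot mothers who used the lesu when settling the child to sleep: 17, stated as 34% (section 1.2).
- Pilot denominator: two pairs were replaced, "bringing the total to 50 participants"; 48 of 50 completed (section 1.2).
- Planned size: 400 pairs, 200 per arm (section 10.2).
- Observation sample: 25% of participants (section 7.1.6).

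**1. The plan's own figure.** 17/50 = 0.340, which matches the stated 34%. Among completers it would be 17/48 = 0.354, so the stated figure uses all 50.

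**2. Its precision.** Exact (Clopper-Pearson) 95% limits:

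- lower: Beta quantile at 0.025 with parameters 17 and 34 = 0.212;
- upper: Beta quantile at 0.975 with parameters 18 and 33 = 0.488.

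**3. Carried to the trial.** Assuming that the pilot share applies to the trial population:

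- per arm: 0.34 × 200 = 68 pairs;
- in total: 0.34 × 400 = 136 pairs;
- across the confidence limits: 0.212 × 400 ≈ 85 to 0.488 × 400 ≈ 195 pairs.

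These counts are ceilings for overnight use. The pilot wording does not separate naps from nights, and the protocol gives no split. If a fraction f of these mothers used the cloth overnight, the expected count is f × 136. With f = 0.5, taken only as an illustration, that is 68 pairs.

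**4. Can another described source record overnight contact?**

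| Source | Who | What the protocol says it covers | Overnight lesu contact |
|---|---|---|---|
| Diary (7.1.5) | all pairs, daily | lesu use in three periods; net use at night; washing | no entry |
| Direct observation (5.9, 7.1.6) | 25% | daytime, chiefly early morning and evening | not covered |
| Bi-weekly questionnaire (2.2, 6.4, 7.1.1) | all pairs | named as a source for 4.C; described only as medical history, symptoms, care-seeking, treatments and adverse reactions | lesu items not shown |
| Cloth punches (covariate 4.D) | lesus | residual permethrin | measures the cloth, not contact |

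The first two exclude it, the third is open, and the fourth does not measure contact.

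**The case against.** The strongest reply is that the diary is not the whole measure. Covariate 4.C also draws on a bi-weekly questionnaire that every pair answers, and the case report forms are held outside the protocol. The pilot instruments did capture blanket use, and Aim 1 says that the trial uses similar methods. This stands. A reader might infer that night contact is lost from the trial altogether, but the documents support only that no source whose content they describe records it.

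Second, the daytime emphasis is deliberate. Section 5.9 targets the hours before people are under the net, section 1.1 presents the lesu as protection against outdoor or daytime biting, and every pair receives a new net. This stands in part. It explains the observation window, but section 7.1.5 gives no such reason for the diary. It also means that contact under a net should not be assumed to carry the same weight as contact outside one.

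Third, the diary item asks about use, not carrying, so a nap under the cloth can be entered in a daytime period. This stands, and it is why 34% cannot be read as the share of unrecorded night use.

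Fourth, fuller diaries burden mothers, whom section 1.2 describes as having relatively little schooling. This stands against a separate child and mother entry in every period. It has little force against a single extra tick.

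**Conclusion.** The gap is real and minor. As described, neither the diary nor direct observation can record overnight lesu contact, although the protocol reports bedding use. At most about a third of pairs are affected: 136 of 400, or 85 to 195 across the pilot's confidence limits. This assumes that the pilot share carries over and that all reported sleep use is overnight, which overstates it to the extent that naps are included.

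The damage is confined to the lesu-use secondary outcome, the low-use trigger and exposure of the as-treated model, and the exploratory use models. The primary analysis compares arms as randomised, whatever the use, so its estimate and power do not change.

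Three stronger readings are tempting, but the documents do not support them:

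- **A stated share of contact hours missed, or of variation in contact unexplained.** The protocol gives no hours of day or night contact and no spread, and the diary records periods rather than hours.
- **Harm to Aim 2 because mother and child share one entry.** No use model specific to mothers is stated. The models in sections 10.3 and 10.3.1 concern the child's primary outcome, and section 10.3.2 offers only contingent sensitivity analyses if adherence is low.
- **Harm to the safety assessment.** Adverse reactions and serious adverse events are summarised by arm, not by recorded use.

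**What to change.** Add one daily yes/no entry to the diary in section 7.1.5: whether the lesu was used overnight as the child's cover or bedding. Count it in the definition of use for covariate 4.C in section 2.2, and in the as-treated and exploratory child models of sections 10.3 and 10.3.1. Report it alongside the nightly net entry, so that overnight use under the net and outside it can be told apart. This would also help to show the change in behaviour listed as a risk in section 1.4.1, where mothers relax net use because they trust the lesu.

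If the bi-weekly questionnaire already has such an item, section 7.1.5 should say so, and the definition of use should name it.

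The cost is a revision of one form before the start and one more tick a day for mothers. No visits, staff or samples are added.

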### Observation logs

Study staff will perform direct observation of a random sample of participants (25%) to document how and when *lesus* are used throughout the day with particular emphasis on the morning and evening periods. Staff will also enquire how participants wash the *lesus* and confirm that LLINs are being used.

### Entomological surveillance

Staff will conduct sentinel surveillance in at least 20% of participant households. Randomization will be in a 1:1 ratio between intervention and control arms with households stratified by village of residence in order to generate high-resolution estimates of mosquito abundance over the study area. Surveillance will occur one night every 2 weeks. To monitor adult mosquitoes, we will employ unbaited (indoor) and CO_2_-baited (outdoor) CDC light traps. All captured mosquitoes will be counted, sexed, and identified to species.

## Laboratory Procedures/Evaluations

### Screening Laboratory Evaluations

- HIV: Testing for HIV will be performed at the household visit with a rapid diagnostic test (SD Bioline HIV-1/2 3.0 Abbott Laboratories, USA) [43]. Approximately 20 µL of whole blood will be collected via finger-prick and placed onto the RDT in accordance with the manufacturer’s instructions.

### Clinical Laboratory Evaluations

- Malaria: Testing for malaria will be performed at the household visit with an RDT (SD Bioline Malaria Ag P.f, Abbott Laboratories, USA or similar pending availability). Approximately 100 µL of whole blood will be collected via finger-prick or heel stick and placed onto the RDT in accordance with the manufacturer’s instructions. This test detects histidine-rich protein II antigen specific to *P. falciparum* malaria. Similar assays are currently employed for routine diagnosis in Uganda [44].
- Hemoglobin: Hb levels will measured at the study clinics using the HemoCue® Hb 201+ analyzer (Brea, California) [45, 46]. Approximately 10 µL of whole blood will be placed onto the microcuvette in accordance with the manufacturer’s instructions. Results are generally available within 1–2 minutes.
- Asymptomatic Parasitemia: DBS will be stored in a mylar bag with desiccant until transport to Epicentre Research Laboratory in Mbarara. *Plasmodium* species DNA will be extracted from DBS using a previously described protocols [47]. The concentration of extracted *P. falciparum* DNA in individual samples will be determined using qPCR for *P. falciparum* lactate dehydrogenase [48].

### Special Assays or Procedures

- Permethrin Concentration: Harvested fabric swatches will be placed in individual mylar bags and stored in an opaque container at 20^o^ C until transport to the [name] Lab at East Carolina University (see attached letter). Swatches will be transferred to individual 60 mL amber glass vials containing 40 mL acetone and soaked for 6 hours to elute permethrin. A portion of the extract (1 pL) will be analyzed directly by capillary GC with flame ionization detector using an Agilent GC 6850 in accordance with previously published protocols [35, 41].

### Specimen Preparation, Handling, and Storage

Information regarding preparation, handling, labeling, and storage of specimens is available in the *Manual of Procedures*.

### Specimen Shipment

Information regarding method and frequency of specimen shipment is available in the *Manual of Procedures*. Transportation of specimens will be recorded in chain-of-custody logs.

# ASSESSMENT OF SAFETY

## Specification of Safety Parameters

Given the established safety of permethrin across applications (e.g., topical, nets, clothing), we anticipate few, if any, adverse events. Therefore, monitoring of any events will be through routine reporting mechanisms. The following measures will be recorded in the study database and will require notification of the PI if exceeding the specified threshold.

| **Parameter** | **Threshold** |
| --- | --- |
| MUAC | MUAC ≤11 cm |
| Hemoglobin | Concentration ≤5 g/dL for children and ≤7 g/dL for adults |
| Skin lesion | Presence of any cutaneous skin lesion or rash |
| Hospitalization | Any reason |

### Unanticipated Problems

Unanticipated problems involving risks to subjects or others include, in general, any incident, experience, or outcome that meets **all** of the following criteria:

- unexpected in terms of nature, severity, or frequency given (a) the research procedures that are described in the protocol-related documents, such as the IRB-approved research protocol and ICF; and (b) the characteristics of the subject population being studied;
- related or possibly related to participation in the research (“possibly related” means there is a reasonable possibility that the incident, experience, or outcome may have been caused by the procedures involved in the research); and
- suggests that the research places subjects or others at a greater risk of harm (including physical, psychological, economic, or social harm) than was previously known or recognized.

### Adverse Events

An adverse event (AE) is any untoward or unfavorable medical occurrence in a human subject, including any abnormal sign (for example, abnormal physical exam or laboratory finding), symptom, or disease, temporally associated with the subject’s participation in the research, whether or not considered related to the subject’s participation in the research.

### Serious Adverse Events

A serious adverse event (SAE) is one that meets one or more of the following criteria:

- Results in death
- Is life-threatening (places the subject at immediate risk of death from the event as it occurred)
- Results in inpatient hospitalization or prolongation of existing hospitalization
- Results in a persistent or significant disability or incapacity
- Results in a congenital anomaly or birth defect
- An important medical event that may not result in death, be life threatening, or require hospitalization may be considered an SAE when, based upon appropriate medical judgment, the event may jeopardize the subject and may require medical or surgical intervention to prevent one of the outcomes listed in this definition.

## Time Period and Frequency for Event Assessment and Follow-Up

Unanticipated problems will be recorded in the data collection system throughout the study. The PI will record all reportable events with start dates occurring any time after informed consent is obtained until 7 (for non-serious AEs) or 30 days (for SAEs) after the last day of study participation. At each study visit, the investigator will inquire about the occurrence of AE/SAEs since the last visit. Events will be followed for outcome information until resolution or stabilization.

